#### The Chinese version of modified Massachusetts General Hospital acupuncture Sensation Scale (C-MMASS)^[26]^

4.3.2

Each patient will be required to complete a C-MMASS form at each end of the acupuncture treatment in order to assess the intensity of the patient's 11 senses: soreness, aching, deep pressure, heaviness, fullness/distension, tingling, numbness, dull pain, warmth, cold, and throbbing.

In order to ensure uniform standards for the trial, the researcher, data collector and statistician responsible for the recruitment must undergo rigorous training before the trial and understand the purpose, contents and quality control of the trial. Detailed evaluation time points are provided in the Figure 3.

### Data management

4.4

Regular monitoring that will be clarified in a standard operating procedure will be conducted at each site to ensure good data quality. The data of the trial needs to be recorded in the CRFs that prepared in both paper and electronic versions. Monitors will audit data every 3 months. During the trial, only the data evaluator can access the CRFs and enter the data in the electronic CRFs. Both the acupuncturist and the data analyst will have no access to these data during the evaluating process. When the trial is completed, the database will be locked by the data management team, after which the researchers can no longer modify the data. Both paper files and electronic documents will be preserved for at least 5 years after publication. If readers and reviewers have any questions, they can contact the corresponding author for access to the original data. Interim analyses will not be undertaken at any time during the whole period of study.

### Ethics

4.5

This study is approved by the Ethics Committee of the First Affiliated Hospital of Henan University of Traditional Chinese Medicine (Ethics Reference No: 2019HL-020–01), and registered in the Chinese Clinical Trial Registry on January 21, 2020, ChiCTR2000029291, http://www.chictr.org.cn/edit.aspx?pid=38787&htm=4. The trial follows strictly the guidelines of the Declaration of Helsinki (Version 2000). Only participates who signed the informed consent form will be included.

### Statistical analysis

4.6

In this trial, we will implement the intention-to-treat analysis and per-protocol (PP) analysis. The intention-to-treat analysis will be used for all allocated participants in the baseline. This trial focuses on the long-term effect of acupuncture, and the observed data will be used as the primary analysis. Primary analysis will be based on intention-to-treat population, including participants with at least 1 assessment of the primary outcome and 1 acupuncture session. Per protocol (PP) analysis will be performed to test the robustness of the primary analysis. PP population will include participants receiving at least 12 sessions of acupuncture and be assessed at week 16.

The demographic and baseline characteristics among 3 groups will be compared using one-way analysis of variance (ANOVA). A χ^2^ test will be used for categorical variables. Due to the occurrence of self-healing tendency in KOA, it is important to testify the existence of the long-term effect of acupuncture effect. The clinical outcomes will be compared among the acupuncture with the *deqi* group, acupuncture without the *deqi* group and the waiting treatment group at every time points (week 0, 4th, 8th, 12th, 16th, 20th, and 24th after randomization) by using the repeated measures ANOVA (3 independent groups with repeated measures).

Clinical outcomes will be analyzed using SPSS 22.0 statistics software (IBM SPSS Statistics, IBM Corp, Somers, NY, USA). Data on Skewed distribution will be normalized. Means, standard deviations, and 95% confidence intervals (CIs) will be used to describe the continuous data. All statistical hypotheses are two-sided tests, and the significance test level α = 0.05, giving the test statistic and its corresponding *P* value, with *P* ≤ .05 as statistically significant. The data will be analyzed by statisticians who are blinded to the test settings. All confidence intervals will be two-sided 95% intervals among the 3 groups (group A, group B and group C).

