1.Recruitment of middle-aged and elderly patients with mild to moderate recurrent knee pain in the past month to avoid the impact of other diseases on pain assessment;2.In order to alleviate patients doubts about different interventions, patients in each group will be treated in different rooms, and patients in each group will be forbidden to talk.3.The acupuncturist is a doctor with more than 6 years of work experience and a medical practitioner certificate. Relevant personnel and data evaluators responsible for recruiting patients are required to undergo rigorous training before the study to ensure that all experimental procedures have uniform standards and avoid observational bias.4.Emotion monitoring. During the whole study, not only the emotional changes of patients will be evaluated on time by the emotion monitoring scales, but also the emotional changes of each patient should be paid close attention in order to eliminate the influence of emotional changes on the disease.

Of course, this study also has some shortcomings, mainly reflected in the following 2 aspects:

1.Because this study has a long observation period, it will result in a higher rate of abscission, which will affect the results of the study. Therefore, we should maintain a good doctor-patient relationship with patients during the study, and the part of the scales involved in this study are self-rating scale, which can be carried out subjectively by patients to better improve the quality of studys data;2.The patients enrolled in this study are limited to mild to moderate KOA patients, so the results of this study have some limitations, they may only be applicable to mild to moderate KOA individuals.

Most domestic and international medical treatment guidelines recommend acupuncture for knee osteoarthritis, but the long-term effect of acupuncture for KOA is not fully defined. Therefore, this study designs a clinical study with a treatment period of 4 weeks and a follow-up period of 20 weeks, aiming to study the long-term effect of acupuncture and the influence of the *deqi* sensation on the long-term in the treatment of KOA, and to provide a clinical basis for treatment of patients with mild to moderate knee osteoarthritis in clinic.

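### Run as a classical repeated-measures ANOVA, the primary analysis drops every patient who misses any of seven visits, which conflicts with the stated intention-to-treat population

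*Protocol article*

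**What the plan says.** Section 4.6 (Statistical analysis) fixes four things that have to fit together.

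- **Data:** "This trial focuses on the long-term effect of acupuncture, and the observed data will be used as the primary analysis". No imputation is mentioned.
- **Model:** the three groups are compared "at every time points (week 0, 4th, 8th, 12th, 16th, 20th, and 24th after randomization) by using the repeated measures ANOVA", described as "3 independent groups with repeated measures".
- **Population:** first, "The intention-to-treat analysis will be used for all allocated participants in the baseline"; then, for the primary analysis, a set "including participants with at least 1 assessment of the primary outcome and 1 acupuncture session".
- **Software:** "Clinical outcomes will be analyzed using SPSS 22.0 statistics software". The procedure within SPSS is not named.

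The only robustness check given is a per-protocol analysis of patients who had 12 or more sessions and were evaluated at week 16. Section 4.1 places the primary WOMAC evaluation at week 16. Section 2.3 allows for 10% dropout. In the Discussion, the authors list the long observation period as a shortcoming: "it will result in a higher rate of abscission, which will affect the results of the study". The responses offered there are good relations with patients and the use of self-rated scales; neither concerns the analysis.

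**The concern.** The population rule admits a patient with one assessment. The named model, in its classical form, can use only a patient with all seven. Every patient between those two extremes belongs to the stated population but not to the fitted model, including some whose week-16 WOMAC was measured.

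Two things are at stake. The first is selection. Nobody receiving or giving treatment is blinded (section 2.5), and group C goes without acupuncture for the whole 24 weeks (sections 2.1 and 3.3), so loss that differs by arm and by symptoms is plausible. A comparison of completers is then no longer the randomised comparison. The second is waste: primary-endpoint values already collected would be set aside because of a missed visit that is not the primary one.

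The per-protocol analysis does not cover this. If it uses the same seven-visit ANOVA, it repeats the same deletion. If it uses the week-16 value alone, it changes the adherence rule and the visit rule together. Neither version shows what missing data do to the result.

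**Working it through.** **Inputs from the article.** Anticipated WOMAC reductions 17 (A), 13 (B) and 8 (C); SD 10; alpha 0.05 two-sided; power 0.90; 99 patients, raised to 108 for 10% dropout (section 2.3). Seven time points: baseline plus six post-baseline visits (section 4.6).

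**Inputs assumed.** Miss rates per visit, dropout above 10% and the dropout mechanism. The article gives none of these.

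**1. The plan's own figure.** I take a one-way omnibus F-test at a single time point. The mean of the three reductions is 38/3 = 12.67, and the sum of squared deviations is 18.78 + 0.11 + 21.78 = 40.67. The noncentrality is n × 40.67/100 for n per arm. This gives power 0.899 at 32 per arm and 0.908 at 33 per arm, so the minimum is 33 × 3 = 99, which matches. For dropout, 99/0.9 = 110 against the stated 108, a difference that does not matter here. This test is the yardstick below because it reproduces the plan; it is not the power of the repeated-measures ANOVA itself.

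**2. Independent misses.** With miss rate q at each of six post-baseline visits, complete rows number 108 × (1−q)^6 and week-16 values number 108 × (1−q). The share lost is 1 − 0.98^6 = 0.114 at 2% and 1 − 0.95^6 = 0.265 at 5%.

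| q (assumed) | All seven visits | Power | Week 16 present | Power |
|---|---|---|---|---|
| 2% | 95.7 | 0.898 | 105.8 | 0.927 |
| 3% | 90.0 | 0.877 | 104.8 | 0.924 |
| 5% | 79.4 | 0.829 | 102.6 | 0.918 |

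At 5%, 102.6 − 79.4, or about 23 patients, have a week-16 value that the model would not use.

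**3. Pure dropout.** With share d gone by week 24 at a constant hazard, complete rows number 108 × (1−d) and week-16 values number 108 × (1−d)^(16/24).

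| d | All seven visits | Power | Week 16 present | Power |
|---|---|---|---|---|
| 10% (article) | 97.2 | 0.903 | 100.7 | 0.913 |
| 20% (assumed) | 86.4 | 0.862 | 93.1 | 0.889 |
| 30% (assumed) | 75.6 | 0.808 | 85.1 | 0.857 |

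With 10% dropout plus 3% intermittent misses at the five earlier visits, 108 × 0.9 × 0.97^5 = 83.5 rows remain and power is 0.849.

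**4. Selection, worst case.** Suppose exactly the worst-responding 10% or 20% of group C leave and nobody leaves A or B. The mean of those who remain rises by φ(1.282)/0.9 = 0.195 SD or φ(0.842)/0.8 = 0.350 SD. At SD 10 that is 2.0 or 3.5 points. Group C's reduction is overstated by this amount, so the planned gaps of 9 (A-C) and 5 (B-C) shrink by it.

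**5. Selection, milder illustration.** In a simulation, the chance of dropout rose with a worse previous score by the same rule in every arm, with within-patient correlation 0.6. The true week-16 A-C difference of 9.0 became 8.3, 8.0 and 7.7 among completers, as completer shares across arms fell from 81–91% to 72–86% to 61–79%. The A-B difference of 4 became 3.8, 3.6 and 3.5.

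**The case against.** The strongest reply is that deletion is inferred. A reader might take the sentence on observed data as a complete-case rule. It is not: it most naturally excludes imputation, and a mixed model is also an analysis of observed data without imputation. The article never says that incomplete patients will be removed, its population rule points the other way, and SPSS can fit a mixed model that keeps partial records. All of this stands, and it makes the point conditional on the model being run as named. It does not remove the point: the text says ANOVA, and classical ANOVA and the stated population do not fit together.

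Three other strong inferences also go beyond the article.

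- **That power falls below plan.** At the only figure given, 10% dropout, it does not (0.903). At 2% misses per visit the shortfall is trivial (0.898). Larger losses rest on assumed rates.
- **That the trial expects high attrition.** The Discussion speaks of a higher rate without a number, and it offers measures to limit the loss.
- **That the per-protocol set is looser on visits and so can never check the primary result.** This holds only if the per-protocol analysis uses a different model, which the article does not say. What holds either way is that it does not isolate the effect of missing data.

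**Conclusion.** The point holds in conditional form and should be corrected; it does not invalidate the trial. The stated population and the stated model conflict. If the model is run as a classical repeated-measures ANOVA, the intention-to-treat analysis is in fact one of all-visit completers. This is a choice made in the text, not a detail left to a statistical analysis plan.

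At exactly 10% pure dropout, power is about 0.90 and the concern is selection. Under assumed independent misses of 2% to 5% per visit, 11% to 26% of patients are lost and power is about 0.90 to 0.83; these figures are illustrative.

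A reader might infer that completer bias would flatter acupuncture. In the scenario considered, with poor responders leaving the waiting list, it works toward the null. The 2.0 to 3.5 points are an upper bound, the milder illustration moves A-C by 0.7 to 1.3 points, and another dropout mechanism could give another direction. The worst case leaves the A-B contrast, the one that isolates *deqi*, unchanged; the milder illustration reduces it by 0.2 to 0.5 points.

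**What to change.** Replace the repeated-measures ANOVA with a likelihood-based mixed model for repeated measures, fitted to all randomised patients with any post-baseline WOMAC. Name the week-16 between-group contrasts as the primary estimates, and align the population definition with that set. The sentence on observed data can stay if it is made clear that it means no imputation. If a mixed model was intended all along, only the wording needs to change.

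The mixed model is valid only under missing at random. A sensitivity analysis that lets dropouts do worse than similar patients who stay, by an amount varied by arm, would be a useful addition. Its detail belongs in the analysis plan, and its absence from the article is not a fault.

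The cost is wording and modest programming, with no extra visits or patients. Section 2.5 keeps the analysts blinded until the analysis is complete, so the change can be fixed before allocation is known.

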### Study design and registration

2.1

This is a parallel-design, randomized controlled trial comparing the therapeutic outcomes of the acupuncture with *deqi* group, the acupuncture without *deqi* group and the waiting-list group. And this trial belongs to the clinical randomized controlled study, which aims to compare the long-term effect of acupuncture treatment among the 3 groups. This trial will be carried out at the Rehabilitation Center of the First Affiliated Hospital of Henan University of Traditional Chinese Medicine, Zhengzhou, Henan, China. The procedure will last for 24 weeks, including a 4-week treatment and a follow-up period of 20 weeks. Patients in *deqi* group and without *deqi* group will receive 20 sessions of acupuncture during the 4-week treatment. The Figure 1 shows the study design in the flowchart, and the Figure 3 illustrates the time schedule of enrolment, interventions, assessments, and visits of participants. The reporting of this trial is conducted according to the Standard Protocol Items: Recommendations for Intervention Trials (SPIRIT) guidelines (Additional file 1).

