### Waiting-list group

3.3

Patients will not receive acupuncture treatment during the trial. These patients will be treated by acupuncture with *deqi* after finishing the trial.

If the patient has pain, bleeding, hematoma or other severe discomfort, the acupuncture treatment should be interrupted and treated immediately. During acupuncture treatment and follow-up, patients are prohibited from using drugs that treat knee osteoarthritis and relieve mood. If necessary, the details of the medication used and dosage of medication used should be recorded in the case report forms (CRFs).

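### The session-based ITT and per-protocol definitions in section 4.6 leave no place for the waiting-list group, and the ITT definition conflicts with another in the same paragraph

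*Protocol article*

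**What the plan says.** The population rules are all in the first paragraph of section 4.6 (Statistical analysis).

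- A general ITT statement: "The intention-to-treat analysis will be used for all allocated participants in the baseline".
- A specific statement of who enters the primary analysis: an "intention-to-treat population, including participants with at least 1 assessment of the primary outcome and 1 acupuncture session".
- The PP rule: "PP population will include participants receiving at least 12 sessions of acupuncture and be assessed at week 16".
- The purpose of PP: "Per protocol (PP) analysis will be performed to test the robustness of the primary analysis".

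The next paragraph compares all three groups, the waiting group by name, using "repeated measures ANOVA (3 independent groups with repeated measures").

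On exposure, section 3.3 says of the waiting-list group: "Patients will not receive acupuncture treatment during the trial". Their acupuncture comes only "after finishing the trial". Section 2.1 says that the deqi and without-deqi groups "will receive 20 sessions of acupuncture during the 4-week treatment", and schedules none for group C.

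**The concern.** A rule that counts acupuncture sessions can be met only by patients who are scheduled to have some. Two of the three arms are, and the waiting list is not. Neither session rule is limited to the needled arms, and neither gives group C a criterion of its own.

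The waiting-list arm matters to the trial's question. Section 4.6 itself refers to a tendency of the condition to improve unaided, and group C is the only arm that shows the course without needling. If the written rules were followed, that comparison would disappear from the primary analysis and from the analysis meant to test its robustness. If they were not followed, the analyst would have to choose between two ITT definitions and invent a PP rule for group C. Who is analysed should not be settled that late, least of all when patients and acupuncturist know the allocation (section 2.5).

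**Working it through.** **Inputs**

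- 108 participants to be enrolled and 99 needed for analysis (section 2.3), allocated 1:1:1 (section 2.4). Planned size per arm: 108/3 = 36 enrolled, 99/3 = 33 evaluable. Section 2.4 describes simple randomisation, so the realised arm sizes may differ somewhat from 36.
- Acupuncture sessions scheduled during the trial: 20 in group A, 20 in group B (section 2.1), 0 in group C (section 3.3).
- Expected WOMAC reductions of 17, 13 and 8 points, SD 10, α = 0.05, power 0.90 (section 2.3).

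**Step 1: apply each rule to each arm**

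| Rule in section 4.6 | A | B | C |
|---|---|---|---|
| All allocated participants | up to 36 | up to 36 | up to 36 |
| At least 1 primary-outcome assessment and 1 session | up to 36 | up to 36 | 0 (has 0 sessions, needs 1) |
| At least 12 sessions and assessed at week 16 | up to 36 | up to 36 | 0 (has 0 sessions, needs 12) |

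The first two rows are both called ITT and differ by the whole of group C: 108 against at most 72. The third row has no alternative wording anywhere in the article.

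**Step 2: does the design depend on group C?**

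The plan's own figure reproduces as a one-way ANOVA on three equal groups.

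- Mean of the expected reductions: (17 + 13 + 8)/3 = 12.67.
- Sum of squared deviations: 4.33² + 0.33² + 4.67² = 40.67.
- Noncentrality with n per arm: n × 40.67/10². For n = 33 this is 13.42.
- Power from the noncentral F distribution: 0.899 at n = 32 and 0.908 at n = 33.

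The first n to reach 0.90 is 33, so N = 99, as stated. With 36 per arm the power is 0.932. The sample size is therefore that of a three-group comparison with group C in it.

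**Step 3: what would remain under the literal rules**

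Only A against B is left, with an expected difference of 17 − 13 = 4 points. Using the normal approximation, power = Φ(4/(10 × √(2/n)) − 1.96):

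- n = 33: Φ(1.625 − 1.96) = 0.37.
- n = 36: Φ(1.697 − 1.96) = 0.40.

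The F test gives 0.36 and 0.39. About 132 per arm would be needed for 90% power. The power of A against B is a separate matter. It is shown here only to size what the literal rule would leave.

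**The case against.** The best defence is that the section shows plainly what is meant. It speaks of all allocated participants, names the waiting group in the ANOVA, and plans confidence intervals for groups A, B and C. On that view the session condition describes the needled arms and an exemption for group C was simply left unwritten. As an account of intent this is persuasive, and a reader who infers that the sponsor plans to discard group C goes further than the text supports. It does not repair the rules. The broad ITT sentence is followed by a narrower one that specifically sets the primary population, and the PP rule has no competing version. The abstract's remark that each patient receives sessions does not help either, because sections 2.1 and 3.3 confine acupuncture during the trial to groups A and B.

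Two stronger readings are tempting and should not be drawn.

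- **That the ITT set is really a week-16 completer set.** A reader might infer this because section 4.1 places the primary evaluation at week 16. With the plan's 10% dropout that would cost 36 × 0.10 = 3.6, or 3 to 4 patients per needled arm. The figure is conditional on taking the primary outcome to mean week-16 WOMAC alone. Section 4.1 names WOMAC itself as the primary measure, section 4.2.1 lists six further WOMAC visits, and asking for at least one assessment suggests several are possible. The PP rule also adds week 16 as a condition of its own, which would be redundant if ITT already required it. The wording is ambiguous, but any WOMAC assessment is the more natural reading.
- **That applying the one-session rule to A and B only would seriously bias the comparison with group C.** It would condition two arms on an event after randomisation and not the third. However, section 2.4 discloses allocation 5 to 10 minutes before treatment, so few patients are likely to be lost before session 1. The bias from this source is probably small.

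**Conclusion.** The point holds as a contradiction in the stated definitions. Section 4.6 contains two incompatible ITT populations and a PP population that no waiting-list patient can enter. Read literally, the session rules exclude all of group C, planned at 36 of 108 participants, from the primary and the robustness analysis. The article states these rules explicitly and they conflict with its own design, so this is not detail that a condensed article leaves to the full protocol or a statistical analysis plan.

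The conclusion rests on two things: group C having no sessions during the trial, which section 3.3 states, and the rules applying to every arm, since no exemption is written. It does not depend on how the assessment condition is read or on any assumed dropout. The loss of 36 patients is what the wording produces, not a forecast. In practice group C will very probably be analysed, under rules the article has not yet given.

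**What to change.** Restate the populations in section 4.6 before the database is locked.

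1. **Primary ITT population:** all randomised participants, analysed in their allocated group whatever number of sessions they received. Delete the one-session condition. State that any available WOMAC assessment contributes to the analysis, so that the assessment condition is no longer open to two readings.
2. **PP population, by arm:** groups A and B with at least 12 sessions and a week-16 assessment, as now; group C with no acupuncture received during the trial and a week-16 assessment. Add that PP is supportive only, because it selects patients on events after randomisation and does so differently in the needled and waiting-list arms.

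The first item needs one check against the rest of section 4.6. A conventional repeated measures ANOVA uses only patients with complete series, so the method named there must be able to use incomplete ones if every available assessment is to count.

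The cost is a few sentences in the protocol or analysis plan, recorded as a dated clarification. No additional patients, visits or data are needed.

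### The per-protocol set, the only stated robustness check, ignores the drug ban in groups A and B and, read literally, contains no waiting-list patients

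*Protocol article*

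**What the plan says.** Section 4.6 (Statistical analysis) fixes the PP population as follows: "PP population will include participants receiving at least 12 sessions of acupuncture and be assessed at week 16". Its purpose is also given: "Per protocol (PP) analysis will be performed to test the robustness of the primary analysis". No other robustness check is named, and nothing in section 4.6 uses medication data in a population definition, a covariate or a sensitivity analysis.

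Section 3.3 (Waiting-list group) contains the rule on drugs: "During acupuncture treatment and follow-up, patients are prohibited from using drugs that treat knee osteoarthritis and relieve mood". The next sentence reads "If necessary, the details of the medication used and dosage of medication used should be recorded in the case report forms". The rule stands under the waiting-list heading, but it speaks of acupuncture treatment, so it is naturally read as covering all arms.

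The same section says of group C: "Patients will not receive acupuncture treatment during the trial".

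Acupuncture is given in weeks 0 to 4 (section 2.1), the primary WOMAC assessment is at week 16 (section 4.1), and patients are not blinded (section 2.5).

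**The concern.** The trial asks whether an effect persists after needling stops. Between the end of treatment at week 4 and the primary assessment at week 16 there are 12 weeks in which the drug ban is the main conduct rule stated for patients. The PP definition tests session attendance, all of it before that window, and presence at its end. It tests nothing in between.

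Two consequences follow. First, in groups A and B a patient who took banned drugs up to week 16 counts as per protocol. If primary and PP results agree, a reader will take that as robustness, although both sets treat medication identically. Second, a rule that demands 12 acupuncture sessions cannot be met by an arm that receives none. For the comparisons with the waiting list, the check cannot be run as written.

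**Working it through.** **1. Who satisfies the PP rule as written**

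| Patient | At least 12 sessions | Assessed at week 16 | In PP set |
|---|---|---|---|
| A or B, no banned drug | possible | yes | yes |
| A or B, banned drug recorded before week 16 | possible | yes | yes |
| C, no banned drug | impossible (0 sessions) | yes | no |
| C, banned drug recorded | impossible (0 sessions) | yes | no |

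The first two rows are treated alike, so PP cannot separate them. The last two leave group C empty, so PP contains only A versus B.

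**2. Planning figures, used only as a yardstick**

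Section 2.3 plans WOMAC reductions of 17, 13 and 8 points with SD 10, two-sided alpha 0.05 and power 0.90, giving 99 patients. A one-way ANOVA F test reproduces this: 33 per arm gives power 0.908 and 32 per arm gives 0.899, so 3 × 33 = 99. The planned differences are A − B = 17 − 13 = 4 and A − C = 17 − 8 = 9. The sample size itself does not bear on this point.

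**3. How far medication could move A − B**

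The documents give no drug effect and no usage rate, so the inputs here are assumptions.

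Shift = (drug effect in users) × (difference in the share of users between the arms).

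- Low: 3 × 0.10 = 0.3 points.
- High: 10 × 0.30 = 3.0 points.

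If use is more common in B, a true 4.0 becomes 4 − 0.3 = 3.7 down to 4 − 3.0 = 1.0. If it is more common in A, it becomes 4.3 up to 7.0. The documents do not say which arm would use more.

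**4. What PP would show**

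Take an assumed 5-point drug effect with 10% users in A and 40% in B, use being unrelated to sessions attended. The expected difference is 4 − 5 × 0.30 = 2.5. A simulation with 33 per arm and 4,000 repetitions gave 2.47 in the full set and 2.47 in the PP set as written. The equality follows from the independence assumption. It illustrates that agreement is uninformative and does not estimate what will happen here.

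**5. What adding a medication criterion would and would not do**

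In the same simulation, excluding users as well returned 4.00, but only because use was unrelated to prognosis. Suppose instead that users would, without the drug, improve g points less than non-users, with arm means unchanged. Non-users then average 13 + 0.40g in B and 17 + 0.10g in A, so the difference among non-users is 4 − 0.30g. With an assumed g = 5 this is 2.5, as far from 4 as the unadjusted result. Exclusion answers a different question; it is not a correction.

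**The case against.** **A condensed article may leave PP exclusions and concomitant medication to an analysis plan that is not shown.** This stands in part. Tabulation and the full list of deviations could well be there, and the definition does not say that its two conditions are the only ones. But the article does state a PP rule, and one of its two conditions cannot be applied to a third of the randomised patients. That is a stated definition fixed badly. If the session condition is shorthand for the acupuncture arms, the silence on drugs may be shorthand too. The remedy in either case is to write the rule out.

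**A reader might infer that heavier drug use on the waiting list shrinks A − C and B − C equally in the primary and PP analyses, so that the two falsely agree.** The text does not support this. Taken literally, PP holds no group C patients, so no such PP contrast exists. The mechanism would apply only if the session rule were meant for A and B alone, which section 4.6 does not say.

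**For A versus B, both arms are needled and the documents give no reason for unequal drug use.** This stands. Patients are unblinded, so a difference is possible, but nothing shows that it is likely or which way it would go.

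**Recorded use may be a tolerated exception.** This also stands. The sentence that follows the ban can be read as allowing use or merely as requiring a record. Calling such patients protocol violators goes beyond the text.

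**Effects of medication taken after randomisation can be part of the effect being estimated.** Agreed, and this is why the primary analysis should stay as it is with respect to medication.

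**Conclusion.** The point holds in a limited form. The PP definition does not reflect the drug ban, so for A versus B its agreement with the primary analysis carries no information about medication use. On a literal reading it has no group C and cannot check A versus C or B versus C.

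The size and direction of any medication effect cannot be derived from the documents. The shift of 0.3 to 3.0 points against a planned A − B difference of 4 rests wholly on assumed drug effects and usage gaps.

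Two stronger conclusions should not be drawn: that the primary result is shown to be biased, or that excluding drug users would recover an unbiased effect. The weakness lies in the only stated robustness check and is cheap to repair.

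**What to change.** 1. Keep the primary analysis regardless of medication use.
2. Apply the 12-session criterion to groups A and B only, so that group C patients assessed at week 16 can enter the PP set. The primary population in section 4.6 also asks for one acupuncture session and needs the same limitation.
3. Add to the PP definition, for all three arms: no recorded use of a prohibited drug between randomisation and week 16.
4. Tabulate recorded use by arm. This is informative whichever PP rule is chosen.
5. Reconcile the ban in section 3.3 with the recording sentence that follows it, and state that it covers all arms if that is meant. Which clinical rule applies is for the investigators.

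The cost is two clauses and one table, using data that the case report form is already meant to hold, provided use is recorded for every patient, including group C. The downside is a smaller PP set whose exclusions occur after randomisation and may depend on pain. It should therefore be labelled a supportive sensitivity analysis and not an unbiased correction.
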